#### Neurobehavioral changes of vocal motor control

The FAF paradigm will be used to measure neurobehavioral changes in auditory-vocal integration in patients with PD before and after TMS intervention, which will reflect their ability to integrate auditory feedback and motor control for speech processing. They will be instructed to produce sustained phonations while exposed to unexpected pitch perturbations in auditory feedback, with vocal and electroencephalographic (EEG) signals recorded simultaneously (see details below). The magnitude and latency of vocal responses will be measured as behavioral responses, while the P1, N1, and P2 components of the event-related potentials (ERPs) will be measured as neurophysiological responses.

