#### EEG data

EEG data will be recorded using a 64-electrode Geodesic Sensor Net (Electrical Geodesics Inc., Eugene, OR, USA) connected to a high input-impedance Net Amps 400 amplifier (Electrical Geodesics Inc., Eugene, OR, USA). The EEG signals will be referenced to the vertex (Cz) and digitally sampled at 1 kHz using NetStation software (v.5.4, Electrical Geodesics Inc., Eugene, OR, USA). TTL pulses will be sent to the EEG recording system via an experimental synch Deutsches Institut für Normung (DIN) for synchronization of voice and EEG signals. The impedance levels of individual sensors will be kept below 50 kΩ throughout the recording, as this amplifier accepts scalp-electrode impedances up to 60 kΩ (Ferree et al., 2001).

The EEG signals will be analyzed offline using NetStation software. They will be band-pass filtered with cut-off frequencies of 1–20 Hz and segmented into epochs ranging from 200 ms before to 500 ms after perturbation onset. An artifact detection procedure will be applied to identify bad trials, during which trials whose voltage values exceed ± 55 μv of the moving average over an 80-ms window will be rejected from further analysis. After re-referencing to the average of the electrodes on each mastoid, artifact-free trials will be averaged and baseline-corrected (−200 ms to 0) to generate an overall ERP response for each condition. A total of 24 electrodes in three regions of interest (ROIs) will be selected for statistical analysis (Dai et al., 2022; Lin et al., 2022): frontal area, including AF3, AFz, AF4, F5, F3, F1, Fz, F2, F4, and F6; fronto-central area, including FC5, FC3, FC1, FCz, FC2, FC4, and FC6; and central area, including C5, C3, C1, Cz, C2, C4, and C6. The amplitudes and latencies of the P1, N1 and P2 components will be extracted from the averaged ERPs for each ROI.

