Statistical Parametric Mapping (v.12.0, Wellcome Trust Centre for Neuroimaging, London, UK) will be used for the preprocessing of rs-fMRI data on the MATLAB platform (MathWorks Inc., Natick, MA, USA). The preprocessing steps will include head motion correction, slice timing correction, spatial normalization, and smoothing. After preprocessing, the REST software (Song et al., 2011) will be used for connectivity analysis of brain functions. Regional homogeneity (ReHo) will be calculated using the Kendall coefficient of concordance (KCC) between the time series of a given voxel and those of its 26 neighboring voxels to reflect the local synchronization of spontaneous brain activity (Zang et al., 2004). ReHo maps between groups will be compared using voxel-wise two-sample *t*-tests in SPM with a significance level of *p* < 0.05. FC, which reflects the temporal correlation of spontaneous brain activity between different regions, will be calculated by Pearson’s correlation coefficient between the time series of a ROI and those of all other voxels in the brain. The right cerebellar hemisphere will be used as the ROI because it has been linked to speech and language functions (Marien et al., 2014; Moberget et al., 2014; Lesage et al., 2017; Argyropoulos et al., 2019; Diedrichsen et al., 2019). The ROI will be centered at MNI coordinate (42, -56, -30) and defined by a sphere with a radius of 6 mm. Correlation coefficients will be transformed to z-scores using Fisher’s r-to-z transformation to obtain z-FC maps for each participant. The contrast between z-FC maps post- and pre-intervention for each participant will be calculated to obtain Δz-FC maps, which will be used for a two-sample *t*-test to compare FC changes between the EG and CG groups. The statistical criterion will be set at *p* < 0.05, and false discovery rate (FDR) will be used for multiple comparisons correction.

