### Statistical analysis

Statistical analyses of clinical and behavioral parameters will be performed using SPSS software (v. 20.0). All patients with PD who have at least one post-intervention assessment will be included in the analysis. Gender differences between groups will be assessed using a chi-square test. Baseline measures will be compared between groups using two-sample *t*-tests. A 2 × 3 two-way repeated-measures analysis of variance (RM-ANOVA) with factors of group (real cTBS, sham cTBS) and time (pre-intervention, post-intervention, 12-week follow-up) will be used to investigate the effects of cerebellar cTBS on speech functions, neurobehavioral changes of vocal motor control, and quality of life. *Post hoc* pairwise correction will be performed using Bonferroni comparison adjustment. Pearson analysis will be used to examine correlations between neurophysiological and behavioral measures. A *p*-value < 0.05 in a two-tailed test will be considered statistically significant.

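### The ERP–behaviour Pearson correlations are judged at an uncorrected p < 0.05, with no pairs named and the handling of arm not stated

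*Protocol article*

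**What the plan says.** The relevant statements in the protocol article are these.

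- Statistical analysis: "Pearson analysis will be used to examine correlations between neurophysiological and behavioral measures". The same paragraph closes with a general rule that a p-value below 0.05 "in a two-tailed test will be considered statistically significant".
- Statistical analysis, on the repeated-measures ANOVA: post hoc "pairwise correction will be performed using Bonferroni comparison adjustment".
- MRI data, closing the comparison of connectivity-change maps: "false discovery rate (FDR) will be used for multiple comparisons correction".
- Neurobehavioral changes of vocal motor control, which uses the same two labels as the correlation sentence. On the vocal side it says: "The magnitude and latency of vocal responses will be measured as behavioral responses". The three ERP components carry the other label, as neurophysiological responses.
- EEG data: "A total of 24 electrodes in three regions of interest (ROIs) will be selected for statistical analysis", and "The amplitudes and latencies of the P1, N1 and P2 components will be extracted from the averaged ERPs for each ROI".

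The article does not say which pairs are correlated, at which of the three assessments, on raw or change values, or whether the arms are pooled, separated or adjusted for. It does not label the correlations exploratory, and it does not list them as a primary or secondary outcome.

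**The concern.** The article names a multiplicity correction for two other analyses and leaves the correlations under the general 5% rule. Many ERP features are available, so some pairs will pass by chance, and the text gives no way to tell a planned finding from a chance one.

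Arm handling is a second source of false links. The Discussion expects cTBS to reduce vocal responses, and it cites earlier work in PD in which both vocal and ERP P2 responses fell after treatment. If both measures move in the treated arm only, a correlation pooled over arms picks up the arm difference even when the two measures are unrelated among patients within an arm.

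These correlations are the only stated test that relates a neural measure to behaviour; the imaging section compares maps between groups. A chance or arm-driven correlation could therefore be reported as a link between neural and vocal response.

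**Working it through.** The article gives no number of correlations and no error rate for them, so there is no stated figure to reproduce.

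**Step 1. Count the pairs.**
- ERP variables (EEG data): 3 components × 2 features (amplitude, latency) × 3 ROIs = 18.
- Narrow reading of behavioural (Neurobehavioral changes of vocal motor control): vocal response magnitude and latency = 2. Pairs per time point: 18 × 2 = 36.
- Up and down shifts analysed separately and matched by direction (Vocal response data): 36 × 2 = 72.
- Broad reading, adding the measures under Voice quality: 2 vocal + about 7 acoustic + 5 GRBAS items = 14. The 7 is an assumption: SPL, fo, MPT and formants (counted as one) for vowels, plus SPL, speech rate and syllable rate for speech tasks. Pairs: 18 × 14 = 252.

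**Step 2. Expected false positives under a global null** = 0.05 × number of pairs. Correlation among the variables does not change this expectation.

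| Reading | Pairs | Expected false positives |
|---|---|---|
| Narrow, directions combined, one time point | 36 | 1.8 |
| Narrow, matched by direction, one time point | 72 | 3.6 |
| Broad, directions combined, one time point | 252 | 12.6 |
| Only 1 to 3 pairs tested | 1–3 | 0.05–0.15 |

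For 36 independent tests, the chance of at least one false positive is 1 − 0.95^36 = 84%. The variables are not independent. In simulation at n = 40 the chance was 63% with assumed correlations of 0.5 among ERP and 0.3 among vocal variables, and 37% with 0.8 and 0.5.

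**Step 3. Effect of pooling arms, if that were done.** Take two arms of 20 (Sample size section), no correlation within arms, and a treatment effect of d SD on both measures. The induced correlation is r = (d²/4) / (1 + d²/4). At n = 40 the test is significant when |r| > 0.312. The values of d are assumptions; the article gives none for these measures. False-positive rates come from 40,000 simulated trials.

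| d | Induced r | Pooled | Adjusted for arm |
|---|---|---|---|
| 0 | 0.00 | 4.9% | 4.8% |
| 0.5 | 0.06 | 6.5% | 4.9% |
| 0.8 | 0.14 | 14% | 5.0% |
| 1.0 | 0.20 | 24% | 4.9% |
| 1.5 | 0.36 | 67% | 5.0% |

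The row d = 0 also describes baseline values, where randomisation leaves no systematic arm difference. Analysing each arm separately would avoid the artefact, but it doubles the number of tests and raises the critical |r| to 0.444 at n = 20.

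**The case against.** The best defence is that this is a journal article about a supportive analysis. Pair lists, time points and covariates for such an analysis are commonly left to a full protocol or analysis plan, which is not shown. The correlations are not a listed outcome. The article ties the neural mechanism mainly to resting-state connectivity, compared between randomised arms with FDR, and the vocal and ERP measures have their own group-by-time ANOVA.

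Much of this stands. That arms will be pooled is not stated, so Step 3 describes a risk the text leaves open and not a planned error. Nor does the text say every pair will be tested; with one to three pairs the multiplicity problem largely disappears.

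A reader might also infer that hundreds of correlations will be declared significant and that the mechanistic conclusion will be full of false links. The article does not support this. Counts in the hundreds need the broad reading of behavioural, or multiplication over shift directions and assessments. Only about 5% of null tests would pass. The mechanistic conclusion does not rest on these correlations alone.

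What the defence does not remove is the decision rule. The section that introduces the correlations also fixes p < 0.05 as significant, and it assigns a correction to the post hoc comparisons but not to the correlations. That is a stated rule, not merely a detail left out.

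**Conclusion.** The point holds in a limited form and is minor. The article applies an uncorrected 5% rule to correlations whose pairs are not named. On its own labels for behavioural and neurophysiological measures, testing all pairs gives 36 per time point and about 1.8 expected false positives under a global null, or 72 and 3.6 if matched by direction. About 250 pairs and 13 false positives follow only if the voice measures are included, with an assumed count of acoustic variables.

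The further inflation from arm depends on three conditions the article does not state: arms pooled, values taken after treatment (or as change), and a treatment effect on both measures. With those it ranges from negligible at 0.5 SD (6.5%) to severe at 1.5 SD (67%), for 40 analysed patients with no within-arm correlation. The between-group comparisons of the primary and secondary outcomes are not affected.

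**What to change.** In Statistical analysis:

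1. Name one or two key ERP–vocal pairs, for example change in P2 amplitude with change in vocal response magnitude, stating the ROI and shift direction. If two are named, say how the 5% is shared between them.
2. Compute them on T1−T0 change as partial correlations adjusted for arm.
3. Apply Benjamini–Hochberg FDR at 5% to the remaining pairs, extending the FDR control already used for functional connectivity, and label those results exploratory.

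This changes analysis wording only; no data collection changes. The cost is that fewer correlations will reach significance. In a family of 36, a lone finding would have to meet 0.05/36 = 0.00139, which for a plain correlation at n = 40 raises the critical |r| from 0.312 to 0.488. The bar is lower when several pairs are related.

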### Data management and monitoring

Data management and monitoring procedures will be implemented to ensure the integrity and security of the collected data. Questionnaires and scales data will be digitalized and stored in a secure file. A second research staff member will verify the accuracy of data entry to avoid errors. EEG, MRI, and other digital data, including output files from computer-based tasks, will be stored on password-protected research computers. Paper-based questionnaires and forms for each participant will be securely stored and sorted by participant ID number for easy access at each stage of the study. Forms containing personal names and data will be stored separately in a locked cabinet. Files containing personal data will be encrypted and accessible only to authorized staff involved in the project. MRI data will undergo pseudonymization to protect participant privacy before analysis.

### Safety

Any adverse events (AEs) that occur throughout the study, whether related to cerebellar c-TBS, MRI scanning, or the rehabilitation program, will be monitored and documented. AEs are defined as any undesirable medical experiences that participants may encounter during the course of the study. Transient head or scalp discomfort and facial twitching in the area of stimulation are the most common AEs associated with TMS. These effects typically resolve once the stimulation is discontinued. Although rare, seizures represent a serious AE that can occur during or immediately following TMS treatment. Seizures are usually brief, lasting less than 1 min (or up to 5 min), and do not typically result in long-term medical complications. All AEs will be reported and documented on the case report form (CRF) by the investigators. Any serious adverse event (SAE) will be promptly reported to the ethics committee, which will determine whether the participant should continue with the intervention. If there is significant deterioration in the participant’s condition, the assigned intervention will be discontinued. Participants who experience harm as a result of their participation in this trial will be provided with appropriate compensation.

## Discussion

This protocol will be the first randomized, sham-controlled trial to investigate the effects and underpinning mechanisms of cTBS over the right cerebellum on speech impairment in PD. The rationale for targeting the right cerebellum with cTBS in this protocol is based on two main considerations. First, the right cerebellum has been implicated in motor aspects of speech and language functions, including articulation, prosody, fluency, and syntax (Marien et al., 2014; Moberget et al., 2014; Lesage et al., 2017; Argyropoulos et al., 2019; Diedrichsen et al., 2019). Second, recent evidence has suggested that cTBS over the right cerebellum can modulate auditory-motor integration for controlling vocal production in patients with SCA, as indicated by reduced vocal compensations for pitch perturbations in auditory feedback (Lin et al., 2022). This protocol will provide novel insights into the potential of cerebellar TMS as a non-invasive and augmentative intervention for speech impairment in PD and contribute to advancing our understanding of the neural mechanisms involved in this intervention.

One important advantage of this protocol is the application of a neuronavigation system for accurate and reliable coil positioning over the stimulation target, namely the VII lobe of the right cerebellum. The precise location and orientation of the coil affect the site and direction of the stimulation, which are critical for the validity and reproducibility of TMS studies. Neuronavigation techniques allows for the precise, consistent, and adjustable targeting of specific brain regions based on individual structural MRI data, thereby enhancing the efficacy, reliability, and safety of TMS interventions. In contrast, previous studies that reported inconsistent effects of rTMS on PD speech disorders (Brabenec et al., 2017) targeted the stimulation site according to the international 10–20 EEG system, a conventional but inaccurate method to guide TMS coil placement based on scalp landmarks. This method may compromise the effectiveness of TMS intervention because it does not account for the anatomical variability of the human brain across individuals, which may influence cortical excitability and stimulation depth. Therefore, the use of neuronavigation techniques is recommended for precise coil positioning in TMS studies. Notably, previous studies targeting specific brain regions in PD using neuronavigation guidance have demonstrated positive outcomes, showing improved levodopa-induced dyskinesias with cTBS over the cerebellum (Koch et al., 2009) and enhanced speech articulation with low-frequency rTMS over the right STG (Brabenec et al., 2019, 2021).

In addition to acoustic and perceptual analyses of speech signals, this protocol incorporates the FAF paradigm to evaluate the effect of cerebellar cTBS on hypokinetic dysarthria in PD in terms of auditory-vocal integration. Coupled with EEG technique, the FAF paradigm measures the vocal and ERP responses to unexpected pitch changes during vocalization, which provides insights into the function of sensorimotor integration for speech processing and may offer greater sensitivity than conventional acoustic and perceptual evaluations for detecting speech impairments. Previous studies have shown that patients with PD have difficulties in integrating auditory feedback with motor systems to properly regulate their vocal production, as evidenced by significantly larger vocal adjustments for and/or greater ERP P2 responses to unexpected pitch or loudness changes relative to healthy controls (Liu et al., 2012; Chen et al., 2013; Huang et al., 2016; Mollaei et al., 2016). More importantly, recent findings have shown auditory-vocal integration in patients with PD can be modulated by SLT or non-invasive brain stimulation, as shown by normalized and reduced vocal and ERP P2 responses to pitch perturbations after LSVT^®^ LOUD (Li et al., 2021) or cTBS over the left SMA (Dai et al., 2022). Notably, patients with PD who underwent LSVT^®^ LOUD exhibited a significant correlation between reduced vocal compensations for pitch perturbations and improved vocal loudness during passage reading (Li et al., 2021). Building on these observations, this protocol hypothesizes that cTBS over the right cerebellum in patients with PD will lead to decreased vocal adjustment in response to auditory feedback perturbations, reflecting their improvement of auditory-vocal integration that enables accurate perception and appropriate correction of errors in vocal output.

This protocol also incorporates rs-fMRI to examine changes in FC between the cerebellum and other brain regions before and after TMS intervention. Rs-fMRI allows for the examination of spontaneous neural activity and functional networks without the need for task performance (Wolters et al., 2019), enabling us to investigate the neural mechanisms underlying the effect of cerebellar c-TBS on speech impairment in PD. Previous studies have shown abnormal connectivity between the cerebellum and other brain regions in patients with PD (Hacker et al., 2012; Wu and Hallett, 2013; Chen et al., 2023), which is correlated to their motor symptoms (Yoo et al., 2019) and speech impairment (New et al., 2015). Moreover, TMS studies on PD have shown significantly correlations between improvement in motor symptoms and changes in functional connectivity (Mi et al., 2020; Tinaz, 2021; Chi et al., 2023). However, few studies have used rs-fMRI to evaluate the effects of TMS on PD speech impairment. Brabenec et al. (2021) found that low-frequency rTMS over the right STG led to improved speech articulation in patients with PD, along with increased FC between the right STG and the left-sided articulatory network. These findings suggest that rTMS may modulate speech function in PD by influencing the FC of the stimulation site with regions of speech-related networks, providing valuable insights into the neural mechanisms of cerebellar c-TBS on speech impairment in PD.

However, this study also has some limitations that should be acknowledged. First, the sample size is relatively small, which may limit the generalizability and reproducibility of our findings. Second, the duration of intervention is relatively short, which may not capture the long-term effects or identify the optimal timing of cerebellar cTBS for addressing speech impairment in PD. Third, complete blinding of participants and assessors may not be possible, as some participants may experience transient side effects or sensations from real c-TBS, potentially influencing their perception of the intervention. These limitations should be addressed in future studies with larger sample sizes, longer intervention periods, and more effective blinding procedures.

## Conclusion

This protocol will provide novel insights into the role of the cerebellum in the treatment of speech impairment in PD and its potential therapeutic benefits. If our hypothesis is confirmed, this protocol will support the notion that cerebellar c-TBS can be a safe, effective, and non-invasive intervention for addressing speech impairment in PD, which can complement or enhance existing behavioral SLT approaches. This protocol will also contribute to advancing our understanding of the neural mechanisms underlying the improvement of speech impairment in PD through the modulation of the cerebello-thalamo-cortical networks using non-invasive brain stimulation techniques. The findings of this study may have important implications for the development of new therapeutic strategies and the improvement of clinical outcomes for patients with PD who suffer from speech impairments.

## Ethics statement

The studies involving humans were approved by the Ethics Committee of The First Affiliated Hospital of Sun Yat-sen University. The studies were conducted in accordance with the local legislation and institutional requirements. The participants provided their written informed consent to participate in this study.
